## 8.2.4 FOLLOW UP DATA COLLECTION

**The secondary outcome** (the need for return to the OR for surgical management of PTH) will be followed for up to seven days after randomization.

**Patient-related outcomes measures (PROM)** include pain (as measured by age-appropriate pain scale) and parental/patient anxiety (measured at 7 days after randomization).  The rationale for measuring parent and child anxiety and pain have been documented as measures that significantly predict overall parent satisfaction with perioperative care^28^. To assess patient and parent-centered outcomes of parental and child anxiety we will assess the following scores at day 7 +/- 1-day post-study drug randomization.

1. PROMIS Short Form v1.0 - Anxiety - 8a 31 May2019, PROMIS Early Childhood Parent Report SF v1.0 - Anxiety 8a - 4-1-2021, and Numeric Rating Scale for Anxiety (NRS-A)
2. Wong-Baker Age-appropriate Pain Score & FLACC Behavioral Assessment Scale

For discharged patients, parents will be contacted by a HIPAA compliant text messaging (e.g., TigerConnect App) or phone call for these assessments and communication. If the patient is still in the hospital, research staff may conduct these follow-ups in person.

Wong-Baker FACES® Pain Score:

[figure not shown]

 FLACC Behavioral Pain Assessment Scale

**Parental and child state and trait anxiety**: To assess anxiety in both parents and pediatric participants, we will use validated Patient-Reported Outcomes Measurement Information System (PROMIS) instruments and a Numeric Rating Scale for Anxiety (NRS-A).

1. PROMIS Anxiety Measures

Older children, adolescents, and parents: Anxiety will be measured using the PROMIS Short Form v1.0 – Anxiety – 8a (31 May 2019). This is an 8-item self-report instrument designed to assess symptoms of fear, worry, hyperarousal, and somatic anxiety over the past 7 days. Items are scored on a 5-point Likert scale (Never to Always). Raw scores are converted to standardized T-scores (mean 50, SD 10), allowing comparison to the U.S. general population. Higher T-scores indicate greater anxiety severity.

Young children (early childhood): For children aged 4–7 years, anxiety will be assessed using the PROMIS Early Childhood Parent Report Short Form v1.0 – Anxiety 8a (April 1, 2021). This parent-reported instrument captures observable anxiety-related behaviors and symptoms in young children. It includes 8 items scored on a 5-point response scale and similarly generates standardized T-scores.

PROMIS measures have demonstrated strong psychometric properties, including good internal consistency, construct validity, and responsiveness across pediatric and adult populations. Use of PROMIS instruments allows harmonization with other clinical trials and facilitates cross-study comparisons through standardized T-score metrics.

2. Numeric Rating Scale for Anxiety (NRS-A): In addition to PROMIS measures, situational anxiety will be assessed using a Numeric Rating Scale for Anxiety (NRS-A). Participants (or parents reporting for young children when appropriate) will rate current anxiety on an 11-point scale from:

- 0 = No anxiety at all
- 10 = Worst possible anxiety

The NRS-A provides a rapid assessment of real-time anxiety intensity and is suitable for use in clinical settings where brevity is required. It has been widely used in peri-procedural and acute care settings and correlates with longer validated anxiety instruments.

Administration Plan

- Parents will complete the PROMIS Anxiety 8a at protocol-defined time points.
- Children ≥8 years of age who are developmentally able will complete the self-report PROMIS Anxiety 8a.
- For children 4–7 years of age, parents will complete the PROMIS Early Childhood Parent Report Anxiety 8a.
- The NRS-A will be administered at predefined peri-procedural time points to capture acute state anxiety.
- All measures may be administered electronically (e.g., REDCap) or via paper forms per site preference.

Rationale: The use of PROMIS instruments ensures standardized, psychometrically robust assessment of anxiety across developmental stages while minimizing respondent burden. The addition of the NRS-A allows efficient capture of acute anxiety changes relevant to procedural timing within the TEAPOT study.

## 8.3 Adverse Events and Serious Adverse Events

### 8.3.1 Definition of Adverse Events (AE)

Adverse event means any untoward medical occurrence associated with the use of an intervention in humans, whether or not considered intervention-related (21 CFR 312.32 (a)).

### 8.3.2 Definition of Serious Adverse Events (SAE)

An adverse event (AE) or suspected adverse reaction is considered "serious" if, in the view of either the investigator or sponsor, it results in any of the following outcomes: death, a life-threatening adverse event, inpatient hospitalization, prolongation of existing hospitalization, a persistent or significant incapacity or substantial disruption of the ability to conduct normal life functions, or a congenital anomaly/birth defect. Important medical events that may not result in death, be life-threatening or require hospitalization may be considered serious when, based upon appropriate medical judgment, they may jeopardize the participant and may require medical or surgical intervention to prevent one of the outcomes listed in this definition. Examples of such medical events include allergic bronchospasm requiring intensive treatment in an emergency room or at home, blood dyscrasias or convulsions that do not result in inpatient hospitalization, or the development of drug dependency or drug abuse. All serious, unexpected, and related adverse events that are unresolved at the time of the subject's termination from the study will be followed by the Clinical Center investigators until the events are resolved, the subject is lost to follow-up, the adverse event is otherwise explained, or has stabilized.

### 8.3.3 Classification of an Adverse Event

#### 8.3.3.1 Severity of Event

For adverse events (AEs) not included in the protocol-defined grading system, the following guidelines will be used to describe severity.

**A. Mild** – Events require minimal or no treatment and do not interfere with the participant's daily activities.

**B. Moderate** – Events result in a low level of inconvenience or concern with the therapeutic measures. Moderate events may cause some interference with functioning.

**C. Severe** – Events interrupt a participant's usual daily activity and may require systemic drug therapy or other treatment. Severe events are usually potentially life-threatening or incapacitating. Of note, the term “severe” does not necessarily equate to “serious”.

#### 8.3.3.2 Relationship to Study Intervention

All adverse events (AEs) must have their relationship to study intervention assessed by the clinician who examines and evaluates the participant based on temporal relationship and his/her clinical judgment. The degree of certainty about causality will be graded using the categories below. In a clinical trial, the study product must always be suspect.

**Probably Related** – There is evidence to suggest a definitive or causal relationship, and the influence of other factors is unlikely. The clinical event, including an abnormal laboratory test result, occurs within a reasonable time after administration of the study intervention, is unlikely to be attributed to concurrent disease or other drugs or chemicals, and follows a clinically reasonable response on withdrawal.

**Potentially Related** – There is some evidence to suggest a causal relationship (e.g., the event occurred within a reasonable time after administration of the trial medication). However, other factors may have contributed to the event (e.g., the participant's clinical condition, other concomitant events). Although an AE may rate only as “possibly related” soon after discovery, it can be flagged as requiring more information and later be upgraded to “probably related” or “definitely related”, as appropriate. This can also include a clinical event, including an abnormal laboratory test result, whose temporal relationship to study intervention administration makes a causal relationship improbable (e.g., the event did not occur within a reasonable time after administration of the study intervention) and in which other drugs or chemicals or underlying disease provide plausible explanations (e.g., the participant's clinical condition, other concomitant treatments).

**Not Related** – A clinical event, including an abnormal laboratory test result, whose temporal relationship to study intervention administration makes a causal relationship improbable (e.g., the event did not occur within a reasonable time after administration of the study intervention) and in which other drugs or chemicals or underlying disease provide plausible explanations (e.g., the participant's clinical condition, other concomitant treatments). The AE is completely independent of study intervention administration, and/or evidence exists that the event is definitely related to another etiology. There must be an alternative, definitive etiology documented by the clinician.

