### 8.3.4 Time Period and Frequency for Event Assessment and Follow-Up

The occurrence of an adverse event (AE) or serious adverse event (SAE) may come to the attention of study personnel during study visits and interviews of a study participant presenting for medical care, or upon review by a study monitor. All serious, unexpected, and related adverse events that are unresolved at the time of the subject's termination from the study will be followed by the Clinical Center investigators until the events are resolved, the subject is lost to follow-up, the adverse event is otherwise explained, or has stabilized.

All AEs including local and systemic reactions not meeting the criteria for SAEs will be captured on the appropriate case report form (CRF). Information to be collected includes event description, time of onset, clinician's assessment of severity, relationship to study product (assessed only by those with the training and authority to make a diagnosis), and time of resolution/stabilization of the event. All AEs occurring while on study must be documented appropriately regardless of relationship. All AEs will be followed to an adequate resolution.

Any medical condition that is present at the time that the participant is screened will be considered as a baseline and not reported as an AE. However, if the study participant's condition deteriorates at any time during the study, it will be recorded as an AE.

Changes in the severity of an AE will be documented to allow an assessment of the duration of the event at each level of severity to be performed. AEs characterized as intermittent require documentation of onset and duration of each episode.

Study staff will record all reportable events with start dates occurring any time after informed consent is obtained for 24 hours for non-serious AEs and 7 days for SAEs after randomization and at the 30-day (+/- 5 days) follow-up phone call for any AEs.  At each study visit, the investigator will inquire about the occurrence of AE/SAEs since the last visit.  Events will be followed for outcome information until resolution or stabilization.

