## 8.4 Unanticipated Problems

### 8.4.1 Definition of Unanticipated Problems (UP)

The Office for Human Research Protections (OHRP) considers unanticipated problems involving risks to participants or others to include, in general, any incident, experience, or outcome that meets **all** the following criteria:

A. Unexpected in terms of nature, severity, or frequency is given (a) the research procedures that are described in the protocol-related documents, such as the institutional Review Board (IRB)-approved research protocol and informed consent document; and (b) the characteristics of the participant population being studied.

B. Related or possibly related to participation in the research (“possibly related” means there is a reasonable possibility that the incident, experience, or outcome may have been caused by the procedures involved in the research); and

C. Suggests that the research places participants or others at a greater risk of harm (including physical, psychological, economic, or social harm) than was previously known or recognized.

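### The causality scale puts the same description of a causally improbable event under both Potentially Related and Not Related, so the categories overlap and the relatedness label has no fixed meaning

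*Protocol*

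**What the plan says.** Section 8.3.3.2 of the protocol defines three grades: *Probably Related*, *Potentially Related* and *Not Related*.

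- *Potentially Related* begins: "There is some evidence to suggest a causal relationship (e.g., the event occurred within a reasonable time after administration of the trial medication". It allows that other factors may have contributed, and says that an event first rated possibly related may later be upgraded to probably or definitely related. Its last sentence reads in part: "This can also include a clinical event, including an abnormal laboratory test result, whose temporal relationship to study intervention administration makes a causal relationship improbable", with other drugs, chemicals or underlying disease as plausible explanations.
- *Not Related* begins with the same description: "a clinical event, including an abnormal laboratory test result, whose temporal relationship to study intervention administration makes a causal relationship improbable". It then adds two conditions: "The AE is completely independent of study intervention administration, and/or evidence exists that the event is definitely related to another etiology" and "There must be an alternative, definitive etiology documented by the clinician".

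Section 8.3.4 makes the relationship to study product a required item on the case report form. Other rules use the word related without tying it to the grades. Section 8.3.2 refers to "All serious, unexpected, and related adverse events that are unresolved" at termination, and Sections 8.3.4, 8.3.7 and 8.4.3 repeat that rule in nearly the same words. One criterion for an unanticipated problem in Section 8.4.1 is "Related or possibly related to participation in the research".

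**The concern.** A causality scale is useful only if each event has one correct grade and each grade means one thing. Here the same description sits in two adjacent grades, and those grades fall on opposite sides of the line between related and unrelated. Two assessors who both follow the text can record different grades for the same event.

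*Potentially Related* also contradicts itself: it asks for some evidence of causality and then admits events whose timing makes causality improbable. A reader of the data could not tell which kind of event a *Potentially Related* entry represents.

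This need not be rare. Adverse events are collected to day 30 +/- 5 (Sections 1.3 and 8.3.5), while Section 8.2.1 describes 24 hours as more than five half-lives of TXA. Many later events could reasonably be judged too late to be drug-related. In children bleeding after recent surgery, the underlying condition will often be a plausible explanation. Because unblinding is not allowed (Section 6.3), assessors have only these definitions and their own judgement.

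**Working it through.** The plan gives no figure to reproduce. The check is a comparison of the two definitions, then a table of which events satisfy each.

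**Step 1: overlap in wording (Section 8.3.3.2, case ignored).**
- Last sentence of *Potentially Related*: 62 words.
- Whole definition of *Not Related*: 90 words.
- Longest identical run: 58 consecutive words.
- 62 − 58 = 4. The only words in the *Potentially Related* sentence outside the run are the four that introduce it.
- 90 − 58 = 32. These remaining words of *Not Related* are its two extra conditions.

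**Step 2: which events meet which definition.** Let T mean that timing makes causality improbable and there is a plausible alternative. Let D mean that a definitive alternative cause is documented. *Not Related* is read as T and D together, since its last sentence is worded as a requirement. The column for *Potentially Related* shows only whether its last sentence is met.

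| T | D | Last sentence of *Potentially Related* | *Not Related* |
|---|---|---|---|
| no | no | not met | not met |
| no | yes | not met | not met |
| yes | no | met | not met |
| yes | yes | met | met |

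With T and D both present, an event fits both grades and the text does not choose between them. With T but not D, only *Potentially Related* is open. On this reading every event that meets *Not Related* also meets *Potentially Related*, but not the reverse.

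**Step 3: the opening test of *Potentially Related*.** Its example of causal evidence is onset within a reasonable time after dosing. The example of improbability in its last sentence is onset outside a reasonable time. One label therefore covers opposite findings on the same criterion.

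**Step 4: what uses the grade.**
- Section 8.3.4: the case report form field is directly affected.
- Sections 8.3.2, 8.3.4, 8.3.7 and 8.4.3: the rule, worded in Section 8.3.4 as "All serious, unexpected, and related adverse events that are unresolved at the time of the subject's termination from the study will be followed", does not say whether *Potentially Related* counts as related.
- Section 8.4.1: possibly related is explained there as a reasonable possibility of causation by the research. *Potentially Related* includes improbable events, so the two terms do not correspond.
- Section 3: the primary safety objective is the incidence of all adverse and serious adverse events. Relatedness does not enter.
- Section 9.4.4: seizure and thromboembolic events are recorded; no analysis by relatedness is stated.

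**The case against.** The best defence is that this is a local drafting slip with few consequences. Much of that stands.

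- **Not every improbable event can be graded either way.** A reader might infer this from the shared sentence alone. The requirement for a documented definitive cause rules it out: without one, *Not Related* is closed. The ambiguity also leans towards attribution to the drug, in keeping with the section's statement that the study product is always suspect.
- **Follow-up does not become arbitrary.** Section 8.3.4 has all adverse events documented whatever the relationship and followed to resolution. Section 8.3.6 has all serious events followed until resolved, chronic or stable. The rule for serious, unexpected and related events lies inside those wider duties.
- **Reporting does not hang on this scale alone.** Section 8.3.6 requires immediate reporting of serious events with its own assessment of reasonable possibility; its exception for endpoint events also has its own causal test. Section 8.4.1 defines its own term and concerns participation in the research.
- **No related-event comparison is planned.** A reader might suppose that one is part of the primary safety objective and quote the shift from regrading one child: 1/6 = 16.7% with 6 children per arm (Section 5.5), or 1/11 = 9.1% with 22 randomised 1:1 (Sections 9.2 and 4.1). These are only the weight of one child in any proportion and do not measure this defect. Since assessors are blinded, inconsistent grading would not by itself favour an arm.

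What the defence does not answer is that a required safety field has grades that are not mutually exclusive, and that one grade mixes improbable events with events showing causal evidence.

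**Conclusion.** The defect is real but contained. The overlap is verbatim, and it leaves two groups of events badly graded: those with improbable timing and a documented definitive other cause, which fit two grades; and those with improbable timing and no definitive cause, which must share a label with events showing causal evidence. The undefined terms possibly related and definitely related add to the confusion.

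The effect reaches the relationship field, any table by relatedness, and the correspondence between the grades and the words related or possibly related in Sections 8.3.2, 8.3.4, 8.3.7, 8.4.1 and 8.4.3. It does not reach total adverse event incidence or the general follow-up duties. No numerical size can be given, because no stated analysis depends on the grade.

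The conclusion assumes that the conditions in *Not Related* are cumulative. If its first two sentences were alternatives and only the last were mandatory, an event with a definitive other cause could be *Not Related* whatever its timing, and the subset relation in Step 2 would fail. The overlap for improbable events with a definitive cause would remain.

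The correction is worth making because it is cheap and concerns safety data in children.

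**What to change.** 1. Move the last sentence of *Potentially Related* into a separate category, *Unlikely Related*, covering improbable timing with a plausible but not definitive alternative. Simply deleting the sentence would not work: such events would fail the evidence test of *Potentially Related* and the definitive-cause test of *Not Related*, and so would have no category.
2. Keep *Not Related* for events with a documented definitive other cause.
3. Use one set of labels throughout, and either remove or define possibly related and definitely related.
4. State which categories count as related in Sections 8.3.2, 8.3.4, 8.3.7 and 8.4.3, and how the grades correspond to the term in Section 8.4.1. Whether *Unlikely Related* falls on the related side should be an explicit decision by the sponsor, since the present text places those events under *Potentially Related*.

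The cost is a short protocol edit, a matching change to the case report form pick-list, and re-grading of any events already recorded. The protocol does not state enrolment status, so the amount of re-grading cannot be judged from it. Sample size, endpoints and planned analyses do not change.

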#### 8.3.3.3 Expectedness

An AE will be considered unexpected if the nature, severity, or frequency of the event is not consistent with the risk information previously described for the study intervention.

### 8.3.4 Time Period and Frequency for Event Assessment and Follow-Up

The occurrence of an adverse event (AE) or serious adverse event (SAE) may come to the attention of study personnel during study visits and interviews of a study participant presenting for medical care, or upon review by a study monitor. All serious, unexpected, and related adverse events that are unresolved at the time of the subject's termination from the study will be followed by the Clinical Center investigators until the events are resolved, the subject is lost to follow-up, the adverse event is otherwise explained, or has stabilized.

All AEs including local and systemic reactions not meeting the criteria for SAEs will be captured on the appropriate case report form (CRF). Information to be collected includes event description, time of onset, clinician's assessment of severity, relationship to study product (assessed only by those with the training and authority to make a diagnosis), and time of resolution/stabilization of the event. All AEs occurring while on study must be documented appropriately regardless of relationship. All AEs will be followed to an adequate resolution.

Any medical condition that is present at the time that the participant is screened will be considered as a baseline and not reported as an AE. However, if the study participant's condition deteriorates at any time during the study, it will be recorded as an AE.

Changes in the severity of an AE will be documented to allow an assessment of the duration of the event at each level of severity to be performed. AEs characterized as intermittent require documentation of onset and duration of each episode.

Study staff will record all reportable events with start dates occurring any time after informed consent is obtained for 24 hours for non-serious AEs and 7 days for SAEs after randomization and at the 30-day (+/- 5 days) follow-up phone call for any AEs.  At each study visit, the investigator will inquire about the occurrence of AE/SAEs since the last visit.  Events will be followed for outcome information until resolution or stabilization.

